## Abstract

**Background:**

Laceback ligatures are passive stainless-steel auxiliaries tied from the first permanent molar hook to the canine bracket during the alignment phase of orthodontic fixed appliance treatment, predominantly in premolar extraction cases. Despite equivocal evidence on their effectiveness in controlling anterior tooth position, lacebacks are routinely used to stabilize flexible nickel-titanium archwires against masticatory forces. Their effects on 3 clinically important outcomes, oral hygiene, appliance complication rates, and patient-reported pain, have never been investigated in a randomized trial, representing gaps explicitly identified in a prior systematic review.

**Objective:**

This study aims to evaluate the clinical and patient-reported outcomes of passive laceback ligatures during the alignment phase of orthodontic fixed appliance treatment, specifically oral hygiene status, archwire and laceback complication rates, and pain.

**Methods:**

This is a single-center, single-blind, split-mouth randomized controlled trial conducted at the Orthodontic Clinic, International Islamic University Malaysia. Eligible participants are patients aged 15 years and older, medically fit with Basic Periodontal Examination scores of 0‐2, requiring full fixed appliance treatment with bilateral premolar extractions and no prior orthodontic treatment. Those with craniofacial deformities, systemic illness, or disability affecting oral hygiene compliance are excluded. Each participant’s oral cavity is randomly allocated using a minimization method, so that one side receives a passive 0.010-inch stainless-steel laceback from the first molar hook to the canine bracket, while the contralateral side receives identical standard fixed appliance treatment (McLaughlin, Bennett, and Trevisi prescription brackets, 0.014-inch superelastic nickel-titanium archwires, and elastomeric modules) without laceback. Outcomes are assessed at baseline (T0), 4 weeks (T1), and 8 weeks (T2) after laceback placement. The primary outcome is the orthodontic plaque index. Secondary outcomes include archwire and laceback complication frequencies and pain assessed by visual analog scale area under the curve. A total of 38 participants provided 85% power to detect a 1-unit orthodontic plaque index difference (*α*=.05). Mixed-model repeated-measures analysis is applied to plaque scores; paired parametric or nonparametric tests to other outcomes. Plaque and archwire assessors are blinded to treatment allocation.

**Results:**

Ethical approval and funding were secured in January 2026. Participant recruitment commenced in February 2026 with a target completion of June 2027. Pretrial examiner calibration achieved satisfactory agreement (interrater Cohen kappa=0.801-0.804; intrarater reliability=0.806-0.862). As of paper submission, 24 participants have been enrolled, and 14 have completed all data collection visits, with no protocol deviations recorded. Primary analysis is scheduled for October 2027; the results are targeted for submission by June 2028.

**Conclusions:**

This protocol describes the first randomized controlled trial to simultaneously evaluate oral hygiene, appliance complication rates, and patient-reported pain associated with laceback use during orthodontic alignment. The split-mouth design controls for interparticipant confounders, and the incorporation of patient-reported outcomes will ensure that findings directly support evidence-based, patient-centered orthodontic practice.

## Introduction

Orthodontic fixed appliances are widely used in orthodontic treatment to correct malpositioned teeth. It involves bonding brackets to the surfaces of the teeth and ligating each bracket to archwires. The preadjusted edgewise appliance, commonly referred to as the straight-wire appliance, incorporates bracket-specific prescriptions for tooth movements in 3 dimensions, thereby reducing the need for complex archwire bending [1]. During the initial alignment and leveling phase, the inherent mesial crown tip incorporated into anterior bracket prescriptions of the preadjusted edgewise appliance may result in forward displacement of the canine crown and consequent proclination of the anterior labial segment. This tendency is particularly problematic in premolar extraction cases, where unsupported spans of archwire and the absence of tooth contact distal to the canines create conditions favoring forward drift of the anterior dentition. To counteract this undesirable tooth movement, laceback ligatures were originally proposed by McLaughlin and Bennett as part of the McLaughlin, Bennett, and Trevisi (MBT)–preadjusted edgewise system. Lacebacks are stainless-steel ligatures, typically 0.009 or 0.010 inches in diameter, tied in a figure-of-eight configuration beneath the main archwire from the hook of the first permanent molar bracket to the canine bracket of the same quadrant [2].

Despite the conceptual rationale for laceback use, the clinical evidence supporting its effectiveness in controlling anterior tooth position remains limited and equivocal. Some researchers reported retroclination of incisors when lacebacks were used [3]. However, usage of laceback is also accompanied by loss of anchorage via mesial migration of molars, indicating a compromise of posterior anchorage rather than a benefit [4]. A systematic review and meta-analysis concluded that the anteroposterior position of incisors and molars was not significantly affected by the use of laceback during the initial phase of orthodontic fixed appliance therapy [5].

The practice of using laceback has not received widespread approval. Nowadays, some clinicians still use lacebacks to support the flexible archwires during early alignment phases of treatment, especially from masticatory forces [6]. Nickel-titanium archwires are superelastic and flexible wires that are routinely used during the alignment stages. However, these wires are characteristically soft and prone to dislodgement from terminal molar tubes or fracture across long, unsupported spans at premolar extraction sites [7]. In order to mitigate such complications, mechanical devices such as bumper sleeves, cinch backs, crimpable stops, and composite stops may be placed at the distal ends of archwires to prevent dislodgement [8]. However, no trials have been conducted to verify this archwire-protective role of lacebacks.

Beyond their purported role in archwire stabilization, lacebacks themselves could be prone to complications such as breakage, dislodgement, and mucosal ulceration [9,10]. Laceback-related complications represent unplanned orthodontic emergencies that necessitate additional clinical appointments and, in general, may be associated with treatment delays. While the overall incidence of appliance breakage during fixed orthodontic therapy has been characterized in recent studies [11,12], evidence specifically addressing the frequency and clinical implications of laceback-related complications remains very limited.

The effect of laceback usage on patient oral hygiene represents a particularly significant and previously unexplored concern. Orthodontic fixed appliances are established plaque-retentive environments that impede effective plaque removal. The figure-of-eight configuration of lacebacks, positioned beneath the main archwire across the buccal segment, creates additional plaque-retentive surfaces and physical obstructions that may further impair toothbrushing efficacy. This can potentially exacerbate enamel demineralization, gingivitis, and the long-term risk of caries and periodontal disease [13]. This concern is amplified by the fact that lacebacks are predominantly applied during the early phase of orthodontic therapy, precisely when patients are still adapting to oral hygiene maintenance around fixed appliances and plaque accumulation is most rapid [14]. Despite this clinically plausible risk, the specific impact of lacebacks on plaque levels and periodontal health has not been studied, as explicitly noted in the systematic review by Fleming et al (2013) [5].

Pain and discomfort represent another important dimension of concern regarding laceback use. Orthodontic pain is the most frequently reported adverse effect of fixed appliance therapy, experienced by up to 90% of patients and particularly pronounced during the initial stages of treatment when orthodontic forces are first applied [15]. Soft tissue trauma from orthodontic appliances, including mucosal ulceration caused by bracket edges, archwire ends, and other auxiliaries, is a common and often painful complication that significantly impacts patient comfort and treatment compliance beyond the discomfort arising from periodontal ligament mechanoreceptors [16]. Pain is now recognized as a critical patient-reported outcome (PRO) that influences treatment compliance, appointment adherence, and overall patient satisfaction [17]. The inclusion of a laceback introduces an additional appliance component that may contribute to soft tissue irritation and pain during the initial adaptation period and may theoretically amplify force transmission to the canine and molar. However, no clinical study has yet examined whether lacebacks are associated with greater pain levels during the alignment phase of fixed appliance treatment.

Currently, despite equivocal evidence regarding the effectiveness of laceback in controlling forward tipping of anterior teeth and risk of posterior anchorage loss, laceback is still routinely used by clinicians in selected cases. In view of the paucity of data on oral hygiene status and patient-reported outcomes following laceback usage, this research aims to evaluate the clinical and PROs of laceback usage during the alignment phase of orthodontic fixed appliance treatment. The specific objectives are to assess the effect of laceback on a patient’s oral hygiene, to investigate the effect of laceback on the frequency of archwire complications, to determine the frequency of laceback complications, and to study the effect of laceback on pain. It is hoped that the results obtained may identify treatments that are both clinically effective and acceptable to patients, as well as provide supportive evidence for clinicians to judiciously weigh the risks and benefits of using lacebacks. The null hypothesis is that there will be no statistically significant difference in clinical and PROs between laceback (intervention) and no laceback (control) groups during the alignment phase of orthodontic fixed appliance treatment.

## Methods

### Study Design

This is a single-center, single-blind, split-mouth randomized controlled trial with a 1:1 allocation ratio for the 2 groups (left and right sides of the oral cavity). In this study, either the left or right side of each participant’s oral cavity is randomly assigned to receive a laceback, while the contralateral side serves as the control (no laceback). The study is aimed to fulfill as many items as possible in the CONSORT (Consolidated Standards of Reporting Trials) 2025 checklist for reporting randomized controlled trials, and the SPIRIT (Standard Protocol Items: Recommendations for Interventional Trials) 2025 checklist for preparing protocols of randomized controlled trials [18,19].

### Clinical Trial Registration

This trial has been registered at ClinicalTrials.gov (NCT07039071), where the protocol and the intended statistical analysis plan can be accessed.

### Study Participants

The target population is orthodontic patients from the Postgraduate Orthodontic Clinic of the Kulliyyah of Dentistry, International Islamic University Malaysia (IIUM). To ensure adequate enrollment, the principal investigator will be actively screening potential participants from the list of orthodontic patients receiving treatment at IIUM. The eligibility criteria are mentioned in Textbox 1.

Textbox 1.Eligibility criteria.
**
*Inclusion criteria*
**

**Patient factors**
Age 15 years and older.Medically fit and well.Good oral hygiene—no dental caries; Basic Periodontal Examination score 0, 1, or 2 in all sextants.
**Orthodontic factors**
Full upper and lower arch orthodontic fixed appliance.Extraction of bilateral upper and lower permanent first or second premolars at least 2 weeks before bond-up.No previous orthodontic treatment.
**
*Exclusion criteria*
**
Craniofacial deformities.Mental or physical disability leading to impaired manual dexterity and difficulty comprehending and following oral hygiene instructions.Underlying chronic medical illness, oral diseases.
**
*Withdrawal criteria*
**
Participants are free to withdraw anytime during the period of study. Reasons for withdrawal will be noted down. Possible criteria of withdrawal include:Serious adverse events arising from laceback, which is very unlikely as it has not been reported in literature.Participant not following study procedures.Participant unwilling to continue orthodontic treatment.

An intention-to-treat analysis is used, whereby data from all participants is analyzed irrespective of any subsequent withdrawal or protocol deviation to ensure that the results will reflect the effects of laceback in a real-world setting, while maintaining the study power because no participants are omitted from the analysis [20,21]. Repeated measures data for plaque score and pain score will be analyzed using a mixed model for repeated measures (MMRM), which accounts for within-participant correlation and handles missing data without formal imputation under the missing at random assumption [22].

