### Intended Statistical Analysis

Statistical analysis is conducted using IBM SPSS Statistics (version 31). Descriptive statistics are used to report participant demographics, baseline characteristics, and frequency of laceback complications. To assess whether the data are normally distributed, interpreting the shape of the histogram and the Shapiro-Wilk test are used. Intra- and interrater reliability for plaque score assessment are measured using Cohen kappa. The threshold for good inter- and intrarater reliability is set to be more than 0.8.

Repeated outcome measurements of plaque scores will be analyzed using a mixed model for repeated measures. The model includes treatment group, time, and treatment-by-time interaction as fixed effects, with participant included as a random effect. A mixed model for repeated measures allows inclusion of participants with incomplete follow-up data without requiring formal imputation, assuming data are missing at random. If the data are not normally distributed, plaque scores over time (T_0_, T_1_, and T_2_) will be compared using the Friedman test.

From the pain diary gathered, the pain scores are plotted against time to allow calculation of area under the curve (AUC) using the trapezoidal rule [34]. Pain AUC will be calculated between T_0_ and T_1_ and T_1_ and T_2_. The mean pain AUC for laceback and no laceback sides will be calculated by averaging pain AUC values between T_0_ and T_1_ and between T_1_ and T_2_. To compare differences in mean pain AUC of laceback and no laceback groups, a paired *t* test is used if data are normally distributed. If the normality assumption is violated, the Wilcoxon signed-rank test is applied instead.

The mean frequency of archwire complications is recorded by summing up the number of complications that happen throughout the study period from T_0_ to T_2_. To compare differences in the mean frequency of archwire complications between the laceback and no laceback groups, a paired *t* test is used if data are normally distributed. The mean frequency of laceback complications and the number and percentage of participants with at least 2 laceback complications are also reported. The value of *P*<.05 is considered statistically significant.

Sensitivity analysis will be conducted by comparing the results of intention-to-treat and per-protocol analyses. If both analyses yield similar results, this demonstrates the robustness and validity of the study’s conclusions.

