When laceback was first introduced, it was intended to counteract the mesial crown tip of the canine bracket and prevent labial segment proclination during the leveling and alignment phase of preadjusted edgewise therapy. Although the effectiveness of laceback in controlling the anteroposterior position of the labial segment has since been disputed, it continues to be used by clinicians for several other purposes, most notably the protection of flexible initial archwires from masticatory forces [6]. The role of laceback in supporting the main archwire, however, remains largely anecdotal. If laceback is demonstrated to reduce the frequency of archwire breakage and dislodgement, it may serve as a valuable tool in minimizing treatment disruptions and unplanned emergency appointments, both of which impose additional costs and inconveniences on patients and clinicians alike. Conversely, if it does not meaningfully contribute to archwire stability, the justification for its routine use would need to be reconsidered.

Orthodontic fixed appliances and their auxiliaries are recognized as plaque-retentive environments, providing additional surface area for biofilm formation and impeding effective oral hygiene. Maintaining adequate oral hygiene is of paramount importance during fixed appliance therapy to minimize iatrogenic complications such as enamel demineralization, dental caries, and periodontal deterioration [35,36]. By evaluating the effects of laceback on a patient’s oral hygiene, this research will provide valuable insights to help clinicians decide whether additional oral hygiene instructions or preventive measures are necessary when using laceback. This will benefit patients by ensuring good oral health throughout the treatment process and contributing to improved overall treatment outcomes.

Furthermore, pain and discomfort are common concerns during orthodontic fixed appliance treatment. As an additional appliance component in direct contact with the canine bracket and molar hook, laceback may contribute to soft tissue irritation, altered force distribution, and heightened sensitivity, particularly during the first days after placement. However, the specific contribution of laceback to pain during the alignment phase has not previously been investigated, leaving clinicians without evidence to inform patient counseling at the time of consent.

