This study also reflects the broader shift in orthodontic research toward patient-reported outcome measures as primary or coprimary endpoints. Recent studies have emphasized that orthodontic evidence should prioritize outcomes that are directly meaningful to patients, not merely clinician-assessed clinical indices [37-39]. By incorporating pain and discomfort as primary endpoints alongside plaque score and appliance complication rates, this trial provides the more comprehensive evidence base required for evidence-based clinical decision-making and patient-centered consent.

Key strengths of this protocol include its randomized split-mouth design, which controls for patient-level confounders; the use of validated and orthodontically appropriate outcome measures (OPI for plaque and Visual Analog Scale for pain); standardized laceback placement verified against a study model prior to commencement; blinded plaque score assessment; and prospective trial registration (ClinicalTrials.gov ID: NCT07039071). The split-mouth design is particularly advantageous in this context because the intervention is strictly localized: the presence of a laceback on 1 side of the mouth does not mechanically or biologically influence plaque accumulation, archwire stability, or pain on the contralateral side, thereby satisfying the key prerequisite for a valid split-mouth trial with negligible carry-across effect.

Several limitations should be acknowledged. First, the single-center nature of this study, conducted within a specialist postgraduate orthodontic clinic, may limit generalizability to primary care settings or to practices using different bracket systems or prescriptions. Second, the inability to blind participants or the treating clinician to the intervention side is an inherent limitation of the split-mouth design; this risk has been partially mitigated by implementing blinded plaque score assessment. Third, the 8-week follow-up period may not capture longer-term changes in oral hygiene adaptation or pain habituation. Fourth, the use of a single operator for laceback placement enhances consistency and reproducibility within this trial, but may restrict external validity across different clinical hands. These limitations will be transparently reported in the subsequent efficacy paper and will be considered carefully during interpretation of results.

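### Pain is given two unranked analyses with different missing-data behaviour, and the Discussion calls it primary although the rest of the protocol makes it secondary

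*Protocol article*

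**What the plan says.** **Analysis of pain.** The intention-to-treat paragraph that closes the eligibility material in Study Participants says: "Repeated measures data for plaque score and pain score will be analyzed using a mixed model for repeated measures (MMRM". It adds that this model "handles missing data without formal imputation under the missing at random assumption", and it defends intention to treat as "maintaining the study power because no participants are omitted from the analysis".

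Intended Statistical Analysis applies the mixed model to plaque only. For pain it says: "From the pain diary gathered, the pain scores are plotted against time to allow calculation of area under the curve (AUC". One AUC is formed for T0 to T1 and one for T1 to T2, the two are averaged for each side, and the sides are compared by a paired t test, or by the Wilcoxon signed-rank test if normality fails. The Abstract agrees with this: mixed model for plaque, paired tests for everything else.

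**Status of pain.** The Abstract says: "Secondary outcomes include archwire and laceback complication frequencies and pain assessed by visual analog scale area under the curve". The Methods headings also place pain under secondary outcomes and plaque under the primary outcome. The Discussion says: "By incorporating pain and discomfort as primary endpoints alongside plaque score and appliance complication rates".

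**The concern.** The two analyses answer different questions unless they are linked. A mixed model of the scores yields a side difference at each time point, while the AUC test yields one difference in time-weighted average pain. They also treat incomplete diaries differently: the model uses whatever readings exist, whereas the paired test needs one finished number per side. Nothing says which result is the pain result.

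Pain is reported by participants who know which side carries the laceback, so freedom to choose its analysis after seeing the data is unwelcome. The conflicting status adds to this. If the Discussion sentence stands in print, a positive pain result could later be presented as a primary finding, although the trial was not sized for pain and states only one unadjusted significance level.

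**Working it through.** **1. The plan's own figure.** Inputs from Sample Size Calculation: difference 1 OPI unit, SD 1.88, α = 0.05, power 85%, dropout 10%. Standardised difference = 1/1.88 = 0.532. A two-sided paired t test (noncentral t) needs n = 34, with power 85.3%. Then 34/0.9 = 37.8, so 38. The stated 34 and 38 reproduce with OPI as the only primary endpoint. No pain effect, SD or power is given.

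**2. The two pain analyses side by side.**

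| | Intention-to-treat paragraph | Intended Statistical Analysis and Abstract |
|---|---|---|
| Data | repeated pain scores | mean of two 4-week AUCs per side |
| Method | mixed model | paired t or Wilcoxon |
| Missing data | missing at random, no imputation | no rule given |
| Main or supportive | not stated | not stated |

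**3. What the paired test needs.** For participant i, D_i = ½(AUC1 + AUC2) on the laceback side minus the same on the other side. Someone who leaves after T1 has no AUC2, so D_i does not exist. That person is either dropped or given a one-period average, and the latter is a further rule. The planned dropout is 38 − 34 = 4 participants. If all four leave before T2, the paired test runs on 34, not 38.

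Missed diary entries come on top. The documents give no rate, so the rates below are assumptions. Entries are taken as independent, and an entry is missed for both sides at once. There are 7 readings per period, hence 14. The lenient rule bridges interior gaps and needs only the last reading of each period: 38 × (1 − p)². The strict rule needs all 14: 38 × (1 − p)^14.

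| p (assumed) | Lenient | Strict |
|---|---|---|
| 1% | 38 × 0.980 = 37 | 38 × 0.869 = 33 |
| 2% | 38 × 0.960 = 36 | 38 × 0.754 = 29 |
| 5% | 38 × 0.903 = 34 | 38 × 0.488 = 19 |
| 10% | 38 × 0.810 = 31 | 38 × 0.229 = 9 |

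The spread shows how much depends on a rule that the paired analysis does not state.

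**4. The two analyses can be joined.** A trapezoidal AUC is a fixed weighted sum of readings, so the mean AUC difference equals Σ w_j (mean laceback score at time j − mean control score at time j). With complete diaries and separate means for each side and time, the model contrast and the average of the D_i are the same number. With gaps, the contrast still uses every reading that was made.

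**5. Status and error rate.** With plaque as the only primary, the primary error rate is 5%. Only if the Discussion were taken literally would it rise: two primaries at 0.05 give 1 − 0.95² = 9.75%, and three (plaque, pain, archwire complications) give 1 − 0.95³ = 14.3%, assuming independence. With Bonferroni, OPI power at n = 34 would be 77.1% (two) or 71.6% (three). The sample size therefore fits pain as secondary and does not support it as primary.

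**The case against.** The best defence is that these are two slips of wording. The dedicated statistical section and the Abstract agree on the AUC test, and the mixed model for pain appears only in a sentence attached to the eligibility criteria. The Abstract, the Methods headings and the sample size agree that plaque is the sole primary, against one Discussion sentence. Rules for incomplete diaries commonly sit in the analysis plan, which the article says is available on the registry and which is not shown here.

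Much of this stands, and it rules out three stronger readings that a reader might infer:

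- **That the AUC test requires complete diaries.** The article gives no such rule. The trapezoidal rule handles unequal spacing and can bridge a missing interior reading, though the area then changes. The strict column above is an illustration and not the plan.
- **That the AUC dilutes the expected effect.** The trapezoid weights over 28 days do put 18% on readings up to day 3 and 82% on those from week 1 to week 4. The Discussion does mention "heightened sensitivity, particularly during the first days after placement", but as general rationale. Its actual pain hypothesis refers to the early weeks, which a 4-week AUC fits. Time weights alone also say nothing about power, which depends on how variable the late readings are.
- **That the trial has a 14% error rate.** That would need the Discussion sentence to override everything else. Laceback complications, moreover, are only described and not tested.

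The defence does not remove the contradiction. The missing-data assurance given for pain belongs to a model that the statistical section does not use for pain. An unseen plan may settle the choice, but this article would still state both.

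**Conclusion.** The point holds as a contradiction in pre-specification of a secondary outcome. Two pain analyses are stated without ranking. The assurance that nobody is omitted is not met by the paired AUC test when a period or a last reading is missing. Planned dropout alone puts up to 4 of 38 participants in that position, if all leave before T2. Any larger loss depends on assumed rates of missed entries and on an unstated rule.

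The primary endpoint label for pain conflicts with the Abstract, the Methods headings and the sample size, and is most likely an error in the Discussion. The plaque analysis, its error rate and the 34/38 calculation are untouched. The matter should be corrected, but it does not threaten the trial's main result.

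**What to change.** Make these changes before allocation codes are released to the analyst. With 24 participants enrolled and 14 completed, the choice is still credible if it is fixed while the analyst is blind.

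1. Name one main pain comparison and keep the estimand of Intended Statistical Analysis: the mean of the T0–T1 and T1–T2 AUCs, laceback side minus no-laceback side.
2. Estimate it as a linear contrast of side-by-time means from the mixed model named in the intention-to-treat paragraph, with the trapezoid weights and the starting value of each period written down. Incomplete diaries then contribute under missing at random.
3. State a parsimonious covariance structure, or fit the model to within-participant side differences. An unstructured matrix for 2 × 14 = 28 readings has 28 × 29/2 = 406 parameters, too many for 38 participants.
4. Keep the paired t or Wilcoxon test on observed AUCs as a sensitivity analysis, with its rule for a missing period or last reading. This also retains a nonparametric check for a bounded score.
5. Correct the Discussion so that OPI is the only primary endpoint and pain and complications are secondary.
6. Add a first-week AUC only as exploratory. Making it the main contrast now would redefine the outcome mid-trial.

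The cost is text edits, a little more modelling work and one stated covariance assumption. No data collection or sample size changes.
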